## Abstract

**Background:**

Most methadone-maintained injection drug users (IDUs) have been infected with hepatitis C virus (HCV), but few initiate HCV treatment. Physicians may be reluctant to treat HCV in IDUs because of concerns about treatment adherence, psychiatric comorbidity, or ongoing drug use. Optimal HCV management approaches for IDUs remain unknown. We are conducting a randomized controlled trial in a network of nine methadone clinics with onsite HCV care to determine whether modified directly observed therapy (mDOT), compared to treatment as usual (TAU), improves adherence and virologic outcomes among opioid users.

**Methods/Design:**

We plan to enroll 80 HCV-infected adults initiating care with pegylated interferon alfa-2a (IFN) plus ribavirin, and randomize them to mDOT (directly observed daily ribavirin plus provider-administered weekly IFN) or TAU (self-administered ribavirin plus provider-administered weekly IFN). Our outcome measures are: 1) self-reported and pill count adherence, and 2) end of treatment response (ETR) or sustained viral response (SVR). We will use mixed effects linear models to assess differences in pill count adherence between treatment arms (mDOT v. TAU), and we will assess differences between treatment arms in the proportion of subjects with ETR or SVR with chi square tests. Of the first 40 subjects enrolled: 21 have been randomized to mDOT and 19 to TAU. To date, the sample is 77% Latino, 60% HCV genotype-1, 38% active drug users, and 27% HIV-infected. Our overall retention rate at 24 weeks is 92%, 93% in the mDOT arm and 92% in the TAU arm.

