### Randomization

Random-number tables are used to allocate subjects to the mDOT intervention arm or the TAU control arm. Randomization is stratified by both HIV status and by HCV genotype, because of the influence of these two factors on virologic outcome. Four distinct randomization lists were created: (1) HIV+, genotype 1 or 4, (2) HIV+, genotype 2 or 3, (3) HIV-, genotype 1 or 4, and (4) HIV-, genotype 2 or 3. To ensure comparison groups of roughly equal size, we randomized by blocks within each of these four strata. In addition, blocks were of variable number to minimize the chance of upcoming group assignment being anticipated by research assistants.

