### Planned statistical analyses

We hypothesize that adherence to ribavirin (measured by pill count) in the mDOT arm will be higher than adherence in the TAU arm, and that the mDOT arm will have a higher percentage of subjects with at least 80% adherence to ribavirin than the TAU arm. Pill count adherence will be treated as a continuous estimate and will be analyzed using linear mixed-effects models to compare mean pill counts between study arms over the course of the trial.

We will also calculate overall ribavirin exposure, which will take into account three factors: percent of prescribed doses taken (adherence), length of time on treatment (persistence), and proportion of the original dose taken (dose reduction) [24]. Ribavirin adherence and exposure will be calculated for each subject during the first 12 weeks, and during the entire 24- or 48-week treatment course (for those who achieve an EVR).

All analyses will be repeated using self-reported adherence, which has been demonstrated to be a valid measure of adherence to HCV therapy [25]. To account for inherent social desirability biases in self-reported adherence, for the majority of these analyses we will dichotomize this variable as 100% vs. <100% [26]. A logistic mixed-effects model will be used to analyze repeatedly measured self-reported adherence.

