**HCV-related Factors**	
HCV genotype, n (%)	
Genotype 1 or 4	24 (60)
Genotype 2	9 (23)
Genotype 3	7 (17)
HCV Viral Load (IU/ml), n (%)	
≥ 800,000 IU/ml	15 (38)
< 800,000 IU/ml	25 (62)
HIV status, n (%)	
HIV-	29 (73)
HIV+	11 (27)
CD4 (cells/mm3), median (IQR)	476 (356 - 820)
Taking HAART, n (%)	7 (64)

a missing data

b depression, anxiety disorder, psychotic disorder, post-traumatic stress disorder, and/or bipolar disorder

The median estimated duration of HCV infection is 10 years (IQR 5 - 18), and 8% of participants had received HCV treatment before. Overall, 60% have genotypes 1 or 4, 23% have genotype 2, and 17% have genotype 3. Among the 11 HIV-infected subjects, 73% have undetectable HIV viral load, the median CD4+ T-cell count is 476 cells/mm^3 ^(IQR 356 - 820), and 64% are on antiretroviral therapy.

Our intervention is feasible and can be implemented in a busy clinical setting. Staff at the DoSA clinics worked collaboratively with the study team, and to date 40 participants have been enrolled from 6 out of 9 clinics. Health care providers communicate well with the Medical Director and research assistants, and nurses at each clinic record daily events on study calendars.

The DOT program is acceptable to our patients. To date, 97% of all patients who were eligible for receiving HCV treatment and met study inclusion and exclusion criteria have chosen to participate. No participants have refused their randomization.

The core components of our DOT program do not require additional funding over existing clinic operating budgets. We do not provide salary support for medical providers, nurses, or support group facilitators. HCV medications are purchased through patients' existing insurance plans, as patients would have initiated HCV treatment even if not enrolled in our study. We do supply pillboxes used for DOT, and we pay the DoSA central pharmacist a stipend to assist with management of subjects in the DOT arm.

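### Comparing ETR and SVR with a plain chi-square test ignores the HIV-by-genotype strata; if those strata are moderately to strongly prognostic, the final test is conservative and loses some power

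*Protocol article*

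**What the plan says.** - **Test.** The abstract of the protocol article (Methods/Design) says that "we will assess differences between treatment arms in the proportion of subjects with ETR or SVR with chi square tests". No strata or covariates are named. The section Planned statistical analyses deals with adherence and ribavirin exposure and adds no virologic analysis.
- **Design.** The section Randomization says: "Randomization is stratified by both HIV status and by HCV genotype, because of the influence of these two factors on virologic outcome". It adds that "Four distinct randomization lists were created" (HIV positive or negative, crossed with genotype 1/4 or 2/3) and that "we randomized by blocks within each of these four strata".
- **Size.** The abstract says "We plan to enroll 80 HCV-infected adults". The section Sample size and power calculations bases the sample size on adherence as the primary outcome and states no power for ETR or SVR.

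**The concern.** The investigators say that HIV status and genotype influence virologic outcome, and they force the arms into balance on both. The arm difference therefore no longer carries the chance imbalance between strata. The Pearson chi-square still counts the between-stratum spread in its variance, as if allocation had been unrestricted. If the strata matter, the standard error is too large, the type I error falls below its nominal level, and the comparison gives up power that the stratified design could have delivered. Better virologic outcome is part of the trial's stated primary objective, and the trial has only 80 subjects, so an avoidable loss is worth removing.

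**Working it through.** The article gives no power or error figure for ETR or SVR, so there is none to reproduce. The check compares the stated test with a stratified one.

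**Inputs from the article**
- Total of 80 (abstract); arms of similar size ("To ensure comparison groups of roughly equal size"), taken as 40 each.
- Genotype: "Overall, 60% have genotypes 1 or 4, 23% have genotype 2, and 17% have genotype 3", so genotype 1/4 is 0.60 and genotype 2/3 is 0.40.
- HIV positive: 11 of 40 (Table 1), or 0.275.

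**Assumptions (not in the article)**
- HIV status and genotype are independent. Table 1 gives only the margins.
- Two-sided 5%, one final test, no continuity correction, common odds ratio 3.5.
- Control (TAU) response rates by stratum, shown as a range.

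**Stratum sizes.** 80 × 0.275 × 0.60 = 13.2; 80 × 0.275 × 0.40 = 8.8; 80 × 0.725 × 0.60 = 34.8; 80 × 0.725 × 0.40 = 23.2. Rounded to even numbers for equal arms: 14, 8, 34 and 24, with weights w = 0.175, 0.100, 0.425 and 0.300.

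**Why the test is conservative.** Under no treatment effect, the chi-square uses variance p̄(1 − p̄) per subject, where p̄ = Σ w·p. With balance forced within strata, the true variance is Σ w·p(1 − p). If R is the ratio of the second to the first, the true size is approximately 2·[1 − Φ(1.96/√R)].

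Strata are listed as HIV+ G1/4, HIV+ G2/3, HIV− G1/4, HIV− G2/3.

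| Strata effects | Assumed TAU rates (%) | p̄ | p̄(1 − p̄) | Σ w·p(1 − p) | R | Approximate size |
|---|---|---|---|---|---|---|
| Mild | 30/45/40/55 | 0.4325 | 0.2454 | 0.2378 | 0.969 | 4.6% |
| Moderate | 20/45/35/65 | 0.4238 | 0.2442 | 0.2177 | 0.891 | 3.8% |
| Strong | 15/50/30/75 | 0.4288 | 0.2449 | 0.1928 | 0.787 | 2.7% |

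For the strong case: 0.1928/0.2449 = 0.787, √0.787 = 0.887, 1.96/0.887 = 2.21, and 2·[1 − Φ(2.21)] = 2.7%.

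**Simulation.** The formula ignores the discreteness of counts, which lifts the actual size slightly. Simulated trials with fixed stratum sizes give:

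| Strata effects | Size, chi-square v CMH | Power at OR 3.5, chi-square v CMH |
|---|---|---|
| Mild | 5.1% v 5.2% | 76.6% v 76.8% |
| Moderate | 4.1% v 4.9% | 72% v 73% |
| Strong | 3.1% v 5.0% | 63% v 69% |

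In the strong case the odds ratio of 3.5 corresponds to overall response of about 43% v 67%. With no strata effect the chi-square has size 5.3%, and at an odds ratio of 3.67 the two tests have equal power (82.2% each).

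**Sensitivity to blocking.** Random stratum sizes with variable blocks of 2 and 4 (block sizes assumed), at an odds ratio of 3.67, give the same picture. Chi-square v CMH power is 74.8% v 76.2% (moderate) and 67.4% v 72.0% (strong), with size 4.3% v 4.9% and 3.1% v 4.9%. With no strata effect, power is 82.3% v 81.4%, so stratifying on uninformative factors costs about one point.

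**The case against.** - **The wording is one clause in a condensed article.** A Mantel-Haenszel test is also a chi-square test, and a fuller plan could specify it. This is possible, but a chi-square on arm proportions is the plain reading and the only virologic test on record. The point concerns a stated test, not a missing detail.
- **The gain may be nil.** This stands. No response rate by stratum appears in the article. Under mild effects the difference is 0.2 points of power (76.8 − 76.6).
- **A reader might infer that the true type I error is below 5% outright.** The article does not support that. With absent or mild strata effects it is about 5.1 to 5.3%. The figures also describe a single final test. The section Approvals and data safety and monitoring requires interim analyses after every twenty patients, with virologic differences as a possible reason to stop. If each of four looks used an unadjusted 5% chi-square with outcomes available, the overall false-positive rate would be about 12.3%, 10.1% and 7.7% under mild, moderate and strong effects. The article does not say how the looks are tested, so that too is conditional.
- **A reader might extend the point to the adherence models.** The plan says pill counts "will be analyzed using linear mixed-effects models to compare mean pill counts between study arms over the course of the trial" and lists no covariates at all, which a condensed article may leave to the full plan. The stated reason for stratifying is virologic outcome, and nothing here was calculated for adherence. The point does not reach that far.
- **Virologic response did not drive the sample size.** This stands and limits the consequence.

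**Conclusion.** The point holds in conditional form and for the virologic comparison only. If HIV status and genotype are moderately to strongly prognostic, as the reason given for stratifying suggests but does not quantify, a single final unadjusted chi-square is conservative and gives up roughly 1 to 6 points of power. If they are weakly prognostic, the loss is negligible. The size rests on the assumed response rates, the assumed odds ratio, and independence of HIV status and genotype. The test remains valid: ignoring the strata does not by itself inflate false positives. This is an efficiency improvement on an outcome for which the trial was not sized.

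**What to change.** Compare ETR and SVR between arms with a Cochran-Mantel-Haenszel test over the four randomisation strata, and report a Mantel-Haenszel risk difference with its confidence interval. The smallest stratum (HIV positive, genotype 2/3) is expected to hold only about 9 of 80 subjects, but the CMH test kept its level at 4.9 to 5.3% in every simulated scenario. The cost is a change of wording in the analysis plan: both factors are known for every subject at randomisation, and no further data or subjects are needed.

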**Discussion:**

This paper describes the design and rationale of a randomized clinical trial comparing modified directly observed HCV therapy delivered in a methadone program to on-site treatment as usual. Our trial will allow rigorous evaluation of the efficacy of directly observed HCV therapy (both pegylated interferon and ribavirin) for improving adherence and clinical outcomes. This detailed description of trial methodology can serve as a template for the development of future DOT programs, and can also guide protocols for studies among HCV-infected drug users receiving methadone for opiate dependence.

**Trial Registration:**

ClinicalTrials.gov: NCT01442311

## Background

Drug users account for a disproportionately large burden of hepatitis C (HCV) infection and have been shown in some studies to achieve HCV treatment success rates that are equivalent to non drug users [1]. However, HCV treatment adherence rates in drug users may be suboptimal in patients who use drugs regularly during HCV treatment [2,3]. Because HCV treatment is most effective when patients adhere to at least 80% of the prescribed treatment regimen [4], interventions to improve HCV treatment adherence need to be developed and evaluated among drug users.

Prior research has shown that treatment adherence for other infectious diseases, such as tuberculosis and HIV, is improved among drug users when directly observed therapy (DOT) is administered at methadone maintenance treatment programs [5,6]. HCV treatment may be well suited for DOT because it has a discrete course lasting 24 to 48 weeks, and the backbone of therapy, subcutaneous pegylated interferon injections, is administered weekly rather than daily. Since methadone-maintained drug users attend opiate agonist treatment programs up to six days per week, it is feasible to observe oral ingestion of daily ribavirin, to which adherence may be particularly important for achieving sustained viral response [7-9]. However, DOT for HCV has only recently been evaluated [10,11], and, to our knowledge, no randomized trial has evaluated both directly observed pegylated interferon and directly observed ribavirin administered on-site in a methadone clinic.

We designed the HCV DOT trial to test the efficacy of modified directly observed HCV therapy provided on-site at a methadone clinic. We implemented this randomized trial in a network of methadone clinics that offers on-site HCV treatment by primary care providers, including standard weekly provider-administered pegylated interferon injections [12-14]. The primary objective of our trial is to determine whether modified DOT (mDOT) with both pegylated interferon alfa-2a plus ribavirin is more efficacious for increasing adherence and improving HCV treatment outcomes than treatment as usual (TAU), which includes weekly provider-administered pegylated interferon and self-administered ribavirin. We here provide a detailed methodological description of this trial, which can serve as a template for other investigators designing HCV DOT trials. In addition, we discuss pertinent safety and logistical issues to guide future studies among HCV-infected drug users receiving methadone for opioid dependence. Finally, we report baseline characteristics of our study population.

## Methods/design

### Study setting

The HCV DOT trial is being conducted in the Division of Substance Abuse (DoSA), a network of nine methadone maintenance clinics administered by the Albert Einstein College of Medicine in the Bronx, New York. Together, these affiliated clinics provide care for approximately 3,500 opioid dependent patients, of whom approximately 65% have been infected with HCV and over 50% have chronic hepatitis C. These nine clinics are the sites for study recruitment, delivery of the HCV DOT intervention, and all research visits.

Substance abuse treatment at each DoSA clinic is delivered by a multidisciplinary staff comprised of substance abuse counselors, nurses, a part-time social worker, a part-time psychiatrist, and a medical team consisting of a physician and at least one physician assistant. The medical team provides comprehensive primary medical care, including HCV and HIV care.

### On-site HCV Treatment Program

HCV-infected patients with appropriate insurance (including Medicaid) are offered on-site HCV evaluation and treatment by primary care providers, and are free to choose whether to receive HCV and other medical care at the methadone clinic or elsewhere. Primary care providers receive ongoing HCV-related training from an internist with expertise in providing HCV treatment to drug users, follow standardized HCV treatment protocols [13,15], and have access to expert backup from a hepatologist. Liver biopsies are available at an off-site affiliated medical center. On-site HCV support groups are available at all nine clinics, and are facilitated by a HCV-infected peer and/or clinic staff [12].

Prior to this trial, most patients received provider-administered pegylated interferon alfa-2a injections (180 mcg weekly), and self-administered twice-daily ribavirin. Ribavirin is taken in three different dosages based on HCV genotype, HIV status, and weight: either 400 mg twice daily, 600 mg in the morning and 400 mg in the evening, or 600 mg twice daily. Among trial participants, those in the TAU arm continue to receive standard treatment (once weekly provider-administered pegylated interferon alfa-2a injections) plus self-administered ribavirin.

Our HCV evaluation and treatment protocol (AASLD 2009) requires assessing HCV viral loads at the following time points: baseline (prior to HCV treatment initiation), after HCV treatment initiation (4 weeks, 12 weeks, 24 weeks, and at the end of treatment) [15], and 24 weeks after HCV treatment completion or discontinuation. The planned duration of treatment is 48 weeks for genotype-1 or -4 monoinfected patients and all HIV/HCV coinfected patients, and 24 weeks for genotype-2 or -3 monoinfected patients. Quantitative HCV viral load is performed by Bayer assay which quantifies viral load between 615-7,700,000 IUs/ml. HCV genotype is assessed prior to treatment initiation. DoSA conducts annual HIV testing for all patients (unless they opt out) who are not already known to be HIV-infected. In addition, patients initiating on-site HCV treatment undergo HIV tests as part of our standard treatment protocol.

#### Trial inclusion and exclusion criteria

Potential trial subjects are eligible for inclusion if they are HCV-infected; receive HCV medical care at the methadone clinic; plan to initiate HCV treatment on-site at the methadone clinic within the next three months; are psychiatrically stable as determined by the HCV treatment provider and/or DoSA on-site psychiatrist; attend their DoSA methadone clinic between three and six days per week to receive methadone; and have been on a stable dose of methadone for two weeks prior to the baseline visit. Participants are excluded if they are unable or unwilling to provide informed consent, are currently receiving HCV treatment (pegylated interferon and ribavirin), or if their primary HCV care provider does not agree to their participation in the trial. Participants are also excluded (and referred immediately to the clinic's medical provider) if they report suicidal ideation during the baseline interview.

### Approvals and data safety and monitoring

The trial was approved by the Committee on Clinical Investigations of the Albert Einstein College of Medicine and the Institutional Review Board of Montefiore Medical Center. All participants provide written informed consent. We are testing a low-risk behavioral intervention that is highly integrated with usual clinical care; for this reason we did not create an independent data safety and monitoring board. Instead we established a data safety and monitoring plan, which requires interim analyses after every twenty patients are enrolled to determine whether there are sufficient risks or benefits, or whether significant differences in virological outcomes between study arms have developed that warrant trial cessation.

### Recruitment

Medical providers are asked to invite all patients initiating on-site HCV treatment to consider enrolling in the trial. Subjects also self-refer after seeing flyers posted in clinics, or are referred by other subjects or through HCV support groups. The initial steps in subject recruitment include a brief screening survey, informed consent, and in depth verification of eligibility using medical records and discussion with providers.

### Randomization

Random-number tables are used to allocate subjects to the mDOT intervention arm or the TAU control arm. Randomization is stratified by both HIV status and by HCV genotype, because of the influence of these two factors on virologic outcome. Four distinct randomization lists were created: (1) HIV+, genotype 1 or 4, (2) HIV+, genotype 2 or 3, (3) HIV-, genotype 1 or 4, and (4) HIV-, genotype 2 or 3. To ensure comparison groups of roughly equal size, we randomized by blocks within each of these four strata. In addition, blocks were of variable number to minimize the chance of upcoming group assignment being anticipated by research assistants.

### Baseline assessment

The baseline assessment consists of an interview, administered using Audio Computer-Assisted Self-Interview (ACASI) technology to reduce social desirability bias. During the interview the subject simultaneously reads the question on the computer screen and listens to it read aloud through headphones. Baseline HCV viral load, genotype, and results of urine toxicology tests are obtained by chart review. All subjects have urine toxicology testing at least monthly, as this is a requirement for methadone maintenance treatment programs. The baseline interview is conducted prior to HCV treatment initiation, and at this visit all subjects are invited to attend HCV support groups. Following completion of the baseline assessment, participants receive their assignment to either the mDOT or the TAU arm.

### Modified DOT intervention arm (mDOT)

Subjects randomized to the mDOT arm receive weekly provider-administered pegylated interferon alfa-2a injections plus modified directly observed ribavirin therapy. We describe this as modified because ribavirin ingestion is observed at the methadone window three to six days per week based on the participants' methadone pick-up schedule, and only one of two daily doses of ribavirin is observed. Our mDOT intervention has 3 additional components: 1) individually packaged take-home ribavirin doses; 2) nurses check in with subjects regarding side effects; and 3) nurses contact on-site medical providers if they note any adherence problems, refusal of ribavirin, or medication side effects.

Preparing pill trays for use in the mDOT intervention requires communication between the trial's Medical Director, research staff, HCV treatment providers, nurses, community pharmacies, and centralized DoSA pharmacists. For each participant, the Medical Director verifies the ribavirin dose by speaking directly with the HCV provider, and calls in prescriptions to a single designated community pharmacy that delivers medications directly to the DoSA central pharmacy. HCV providers are asked not to write ribavirin prescriptions for mDOT participants for the 24-48 week HCV treatment period, and to contact the Medical Director directly if a participant changes dose or discontinues ribavirin.

To minimize nursing burden, all DOT medications are prepared in advance in individualized pill trays. Pill trays are labeled by research assistants and filled by centralized DoSA pharmacists. Each pill tray holds seven removable single dose pillboxes that contain ribavirin pills. Since ribavirin is prescribed twice daily, we utilize two pill trays: one containing the morning doses (usually 2-3 capsules) and one containing the evening doses (usually 2-3 capsules). Depending on methadone pick-up schedule and dosing frequency, certain doses cannot be observed (i.e., weekend doses, evening doses, and doses to be taken on a non-clinic day). In these instances, participants are given single dose pillboxes, or "take home doses," for each unobserved dose, and are asked to return the pillbox to the nurses at the next clinic visit, whether or not they have taken the pills. Pill trays are delivered from the centralized DoSA pharmacy to the individual methadone clinics every two weeks, along with scheduled methadone deliveries. Nurses instruct the subjects to eat food soon after ingestion of ribavirin, and snacks are available at the nursing station.

